##### Participants

The target population of this study is farmers with hypertension from 3 PHCs in Jember, East Java, Indonesia. Three PHCs have been chosen to represent the characteristics of agricultural areas with a high hypertension problem. The 3 PHCs have implemented the Integrated Health Program (IHP) for NCDs.

##### Inclusion and Exclusion Criteria

The inclusion criteria are as follows: farmers aged 45-65 years with stage I hypertension (systolic blood pressure [SBP]: 140-159 mmHg and diastolic blood pressure [DBP]: 90-99 mmHg) according to the JNC VIII criteria, farmers performing appropriate work, and those providing a commitment to attend the study for 3 months. We will exclude those who have experienced stroke as they are not eligible for participation, those with hypertension of stage II or higher, those taking medications, and those who have been hospitalized.

##### Sample Size Determination

The sample size will be determined using a traditional sample size calculation based on the McNemar test. The sample size in the McNemar test in this study should fulfill the following criteria: (1) directional hypothesis for 1 tail; (2) magnitude of expected change using the odds ratio (OR; OR=2); (3) alpha value of .05; and (4) required power of 0.8 or higher. The OR and the proportion are expected to change as a result of the intervention. Considering a 2-tailed approach, an effect size of 2.0 at an α value of .05 and power of 80%, and a change in 75% of the population as a result of the intervention, 96 participants would be needed to detect the effect.

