##### Data Analysis Plan

SPSS version 22.0 (IBM Corp) will be used for the analysis. The significance level will be set as *P*<.05. Numerical data will be presented using means and standard deviations, while categorical data will be presented using frequencies and percentages. Furthermore, a linear generalized estimating equation (GEE) will be used to estimate the parameters of a generalized linear model with a possible unmeasured correlation between observations from different timepoints for SBP and DBP (comparing pretest and posttest).

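### The trial's 96 participants are sized for a one-sample McNemar test, so the stated 80% power does not apply to the two-arm comparison of blood pressure

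*Protocol article*

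**What the plan says.** Under Activity 3, the Sample Size Determination section states: "The sample size will be determined using a traditional sample size calculation based on the McNemar test". Its listed criteria include a "directional hypothesis for 1 tail", an odds ratio of 2, an "alpha value of .05" and "required power of 0.8 or higher". The result is then given on a different sidedness: "Considering a 2-tailed approach, an effect size of 2.0 at an α value of .05 and power of 80" percent, and "a change in 75% of the population as a result of the intervention, 96 participants would be needed to detect the effect". The section names no yes/no endpoint, does not say whether 96 is a total or a number per arm, and mentions no loss to follow-up.

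The rest of Activity 3 describes another kind of comparison:
- **Design:** two groups, randomly allocated, with a pretest and a posttest.
- **Outcome Measures:** SBP and DBP are the main outcomes, also to be classified by the JNC VIII criteria.
- **Data Analysis Plan:** "a linear generalized estimating equation (GEE) will be used to estimate the parameters of a generalized linear model", applied to SBP and DBP.
- **Inclusion and Exclusion Criteria:** entry is limited to "farmers aged 45-65 years with stage I hypertension".

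**The concern.** A McNemar calculation needs two inputs: the proportion of pairs that change, and the ratio of changes in one direction to changes in the other. It answers whether one set of people changed between two occasions on a yes/no variable. A randomized two-arm trial with a continuous outcome needs a between-arm difference, a standard deviation and a number per arm, and none of these appears.

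The power statement therefore belongs to a test that the protocol does not plan. A pre-post change in one sample also cannot separate the diet from the health education session given to both arms, or from the fall in readings expected when people are selected for raised pressure. If the paragraph stands, the trial will be reported as having 80% power when no one has worked out its power for SBP or DBP.

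**Working it through.** **1. Reproduce the stated figure.** Inputs from Sample Size Determination: odds ratio ψ = 2, proportion changing p = 0.75, alpha .05, power 0.80. Normal quantiles: 1.960 two-tailed, 1.645 one-tailed, 0.8416 for power.

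n = [z_α(ψ+1) + z_β·√((ψ+1)² − (ψ−1)²p)]² / [(ψ−1)²p]

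- Two-tailed: (1.960×3 + 0.8416×√8.25)² / 0.75 = 91.8, so 92.
- Two-tailed with continuity correction, adding 1/|0.50 − 0.25| = 4: 95.8, so **96**, as stated.
- Two-tailed exact test: first N with at least 80% power is 99; power at 96 is 78.9%.
- One-tailed: 72.1, so 73 uncorrected; 76 to 77 corrected; 79 exact.

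The 96 is thus a two-tailed, continuity-corrected, single-sample McNemar number. No one-tailed version gives 96.

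**2. What the inputs imply.** With ψ = 2 and 75% changing, 0.75 × 2/3 = 50% change in one direction and 0.75 × 1/3 = 25% in the other. If the unnamed endpoint is hypertension status, the 25% would be people moving from not hypertensive to hypertensive. Everyone is admitted with stage I hypertension, so a cell of that size is implausible.

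**3. Set the calculation beside the trial.**

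| | Sample size paragraph | Rest of Activity 3 |
|---|---|---|
| Comparison | paired change, one sample | two randomized arms |
| Outcome | yes/no, not named | SBP and DBP |
| Test | McNemar | linear GEE |
| Effect | odds ratio 2 | no mmHg difference or SD given |

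**4. What 96 delivers for a difference in means.** Assumptions, none stated in the document: 96 is the total and allocation is 1:1, so 48 per arm. Two-sided alpha .05, power 80%.

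Detectable difference = (1.960 + 0.8416) × SD × √(2/48) = 0.572 SD.

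| Assumed SD (mmHg) | 48 per arm | 38 per arm (assumed 20% loss) |
|---|---|---|
| 8 | 4.6 | 5.1 |
| 10 | 5.7 | 6.4 |
| 12 | 6.9 | 7.7 |

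The last column uses 2.8016 × √(2/38) = 0.643 SD.

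Baseline adjustment multiplies the detectable difference by √(1 − ρ²), where ρ is the pre-post correlation. For assumed ρ of 0.3, 0.5 and 0.7 and 48 per arm, this gives 0.55, 0.50 and 0.41 SD; at SD 10 that is 5.5, 5.0 and 4.1 mmHg.

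**5. Sensitivity to the missing target.** For an assumed 5 mmHg difference, unadjusted, the total needed for 80% power is 82, 126 or 182 at SD 8, 10 or 12. The stated 96 lies inside that range.

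**The case against.** The strongest defence is that 96 is correct for the inputs given. That stands. A reader might infer an arithmetic error from the uncorrected 92 or from the exact power of 78.9% at 96, but these only reflect other versions of the same test.

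A reader might also call the 25% cell impossible. The document does not establish this. The yes/no endpoint is not named, and acceptability of the diet, also listed as a trial outcome, could change in both directions. Even for hypertension status, data are taken at registration, pretest and posttest, and the text does not say which reading settles eligibility. Someone could read below the threshold at pretest and above it at posttest. Implausible is as far as the text goes.

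Nor can the 50% and 25% be read as response rates in the two arms and used to compute a power. They are two cells of one paired table, and nothing in the article presents them as arm proportions.

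The conflict between one tail and two tails has no numerical effect, since only the two-tailed version gives 96. It is a wording fault.

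Finally, the Data Analysis Plan speaks only of comparing pretest and posttest. The between-arm contrast is inferred from the randomized design and the aim of testing effectiveness, which is a secure inference. None of these points carries the 80% over to that contrast. Nor does condensation into an article explain the problem: the method is stated, and it conflicts with the stated design, outcome and analysis.

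**Conclusion.** The point holds as a mismatch between the sample size calculation and the trial. The 80% power does not apply to the comparison of SBP or DBP between arms, and this conclusion needs no assumption beyond the article's own text.

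Its size can be given only conditionally. With 48 per arm (assumed), 80% power requires a true difference of about 0.57 SD unadjusted, or 0.55 to 0.41 SD with baseline adjustment at an assumed correlation of 0.3 to 0.7. With an assumed 20% loss it is about 0.64 SD unadjusted. Limitations of the Study expects dropout but gives no rate.

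A reader might infer that 96 is too few. The document does not support that, nor that 96 is enough: either claim needs a target difference and an SD that it does not give.

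**What to change.** Replace the McNemar paragraph with a two-sided, two-sample calculation for the between-arm difference in posttest SBP and in posttest DBP, each adjusted for its baseline value. State the target difference, SD, pre-post correlation and expected loss, with a source for each. Say whether 96 is the total and give the number per arm. Delete the one-tail criterion and the claim of 80% power for an odds ratio of 2.

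If 96 is kept, for example because it is what recruitment allows, say so and report the difference in mmHg that it can detect. A detectable difference worked back from a fixed number describes the trial but does not by itself justify the number.

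The cost is one rewritten paragraph. The restated figure may look less favourable. Whether more participants are needed depends on the target and SD chosen.

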##### Randomization

Initially, public health nurses (PHNs) will visit the study areas and make announcements about the study for farmer participation. The recruitment will be open for 6 months. Farmers will visit the PHC and will be provided an explanation of the study. Informed consent will be obtained, and farmers will be randomized using a computer-generated number. The allocation sequence will be concealed from the researchers and farmers. The computer-generated number system will randomize the initial name of the farmers from the PHC. The PHNs from the PHC will then obtain informed consent and manage the study groups.

##### Outcome Measures

The main outcome measures in this study are SBP and DBP, which will be measured using a standard protocol employing a stethoscope and sphygmomanometer after stabilizing subjects for more than 10 minutes. Measurements of SBP and DBP (mmHg) will be categorized according to the JNC VIII criteria to determine hypertension for participants aged >18 years [24]. The length of work per day, time of rest during working, and hours of sleep per day will be assessed among the farmers. These factors will be measured as they can influence blood pressure among farmers, according to a previous study [2]. Manual blood pressure measurement is usually performed using a mercury device or a calibrated needle (aneroid). SBP and DBP are determined through auscultation by listening for the appearance and disappearance of Korotkoff sounds in the brachial artery. Blood pressure measurements will be taken after a 14-minute rest period, during which the researcher and the participant will have a conversation to reduce tension associated with the “white coat” effect. Measurements will be taken at the same time (ie, 8 AM before activities) with the same tool. Participants will be told not to wear clothes that are too thick. Blood pressure test results will be more accurate if the cuff is placed directly over the skin. Participants will be told to empty their bladder before measurement. For the measurement, participants will be told to sit with their arms on a table so that the elbows are in line with the heart, the back is well supported by the back of the chair, and the feet are on the floor.

##### Data Collection Plan

At baseline, sociodemographic data, including age, gender, education level, smoking, hours of work, rest during working, and hours of sleep per day, will be obtained using a self-administered questionnaire. For measuring SBP and DBP at the PHC, participants will sit in a chair and relax for 10 minutes. Then, PHNs will measure blood pressure at least twice. If the blood pressure values obtained in the second measurement differ from the values in the first measurement by ≥10 mmHg, a third measurement will be carried out. The 2 measurement values with the smallest difference will be averaged to obtain the final value [24].

##### Intervention Group Arm

The intervention group will receive a community-based intervention program involving a PBD.

##### Control Group Arm

The control group will receive a standard education intervention through the IHC for NCDs and available health services that can be accessed every month in the community.

##### Intervention

The intervention group will receive a PBD formulated by the researchers. Farmers will consume the plant-based food 3 times per week. For the PBD, we will adopt a standard protocol from previous studies [1]. Therefore, we have decided to provide the PBD for 6 months.

In the control group, participants will receive education on health and safety on attending the IHP for NCDs, and they will adopt healthy behaviors according to the health education. As they will receive health education, they will be able to lead a healthy life in the agricultural environment, with occupational health and safety.

In both study groups, health education will be provided before the program, which will include information on how to manage a healthy lifestyle while working as farmers, including diet, exercise, rest, and sleep, and how to address blood pressure problems among farmers. Participants will receive this health education in a single session for 60 minutes at the first screening meeting. All participants will receive a manual book on a healthy lifestyle in an agricultural setting.

The blood pressure of participants in both study groups will be maintained. If the blood pressure increases to hypertension stage II or above, appropriate treatment will be provided by the medical doctor in the PHC and the participant will be excluded from the study. Data will be obtained at registration and at the pretest and posttest assessments. For blood pressure data, we will use rounded values, with values ending in 0-4 being rounded to “0” and values ending in 6-10 being rounded to “10” (eg, 120-124 mmHg will be rounded to 120 mmHg, 125 mmHg will be used directly, and 126-130 mmHg will be rounded to 130 mmHg).

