### Limitations of the Study

This study will examine the effectiveness of a community-based nursing program for the management of hypertension using a PBD among farmers in Indonesia. However, this protocol may have some limitations. First, the program requires participant compliance for carrying out regular training to maintain blood pleasure, and some participants may drop out of this study for various reasons, such as noncompliance with the consumption of a PBD. Therefore, a dairy is required to continuously monitor the diet. Second, the measurement of blood pressure may be biased because of different enumerators and sphygmomanometers. This can be minimized by interrater enumerator measurements and instrument calibration.

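### Removing participants whose blood pressure rises to stage II deletes randomised people on the value of the main outcome; if the diet works, the estimated effect shrinks toward zero

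*Protocol article*

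**What the plan says.** All references are to the protocol article, Activity 3.

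- **Intervention**, for both groups, if pressure rises to stage II or above: "appropriate treatment will be provided by the medical doctor in the PHC and the participant will be excluded from the study".
- **Outcome Measures**: "The main outcome measures in this study are SBP and DBP".
- **Inclusion and Exclusion Criteria**: entry requires stage I hypertension, SBP 140-159 and DBP 90-99 mmHg. Stage II or higher is an exclusion.
- **Intervention**, on timing: "Data will be obtained at registration and at the pretest and posttest assessments". The number and timing of any other pressure checks are not given.
- **Data Analysis Plan**: "a linear generalized estimating equation (GEE) will be used to estimate the parameters of a generalized linear model", comparing pretest with posttest.
- **Sample Size Determination**: 96 participants, with no stated allowance for removals.

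No section keeps a removed participant in follow-up, collects their posttest reading or returns them to the analysis.

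**The concern.** The variable that triggers removal is the variable the trial is meant to compare. Removal happens after randomisation, and the threshold lies directly above the entry range, so ordinary variation in pressure will carry some participants across it.

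The participants lost are those with the highest readings. If the diet works, there are more of them in the control arm. The control mean then falls by more than the intervention mean, and the difference between arms narrows. Those who remain were selected after randomisation, so the comparison is no longer protected by it. The analysed sample also falls below 96, which costs power on top of the attenuation.

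This is not a detail that an analysis plan could settle later. The protocol fixes the removal itself, and a posttest value that was never taken cannot be recovered at analysis.

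**Working it through.** **1. The plan's own figure.** The stated 96 (McNemar, OR 2, 75% changing, two-tailed 0.05, power 80%) reproduces:

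n = [1.96(OR+1) + 0.8416·√((OR+1)² − (OR−1)²·0.75)]² / [(OR−1)²·0.75] = 91.8.

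The difference in discordant proportions is d = 0.75·(2−1)/(2+1) = 0.25. With continuity correction, n/4·[1 + √(1 + 2/(n·d))]² = 95.75, that is 96. The figure contains no margin for removals.

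**2. Inputs for the bias.** From the protocol: entry 140-159/90-99 mmHg, and removal at stage II. Stage II is read here as SBP ≥160 or DBP ≥100, the values just above the stated stage I range. Everything else is assumed, because the protocol gives no SD, effect in mmHg or removal rate: true effect 5/3 mmHg, one check, equal detection in both arms, 1:1 allocation.

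**3. A hand check, SBP limb only.** Let posttest SBP = 148 − effect + 0.5·(baseline − 150) + error with SD 10, and baseline uniform on 140-159 (mean 149.5, SD 19/√12 = 5.48).

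- Control mean 148 − 0.25 = 147.75. Intervention mean 142.75.
- Total SD = √(10² + (0.5·5.48)²) = 10.37.
- Mean of those kept ≈ μ − σ·φ(a)/Φ(a), with a = (160 − μ)/σ.
- Control: a = 1.181, removed 1 − 0.881 = 12%, mean kept 147.75 − 10.37·0.2254 = 145.41.
- Intervention: a = 1.663, removed 1 − 0.952 = 5%, mean kept 142.75 − 10.37·0.1051 = 141.66.
- Estimated effect 145.41 − 141.66 = 3.75 instead of 5 mmHg, a loss of 25%.

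**4. Both limbs, by simulation.** Same SBP model. DBP is analogous (centre 94.5, error correlation 0.6). Arms are compared on posttest SBP among those kept.

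| Error SD (SBP/DBP) | Control fall | Baseline | Removed, control vs intervention | Estimated SBP effect (true 5) |
|---|---|---|---|---|
| 12/8 | 2/1 | uniform | 29% vs 17% | 3.2 |
| 10/6 | 2/1 | uniform | 21% vs 9% | 3.45 |
| 10/6 | 6/3 | uniform | 12% vs 4.5% | 3.95 |
| 10/6 | 6/3 | skewed to 140/90 | 9% vs 3% | 4.15 |
| 8/5 | 6/3 | skewed to 140/90 | 5% vs 1% | about 4.6 |

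A slightly higher DBP centre takes the top row to about 3.1 (a loss of 37%). The bottom row is a loss of about 8%. Comparing changes from pretest instead of posttest values trims the loss slightly (3.56 against 3.45 in the second row). With everyone kept, 5.0 is recovered.

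**5. A second model.** Here true pressure varies between people (SBP SD 10), readings vary within people (SD 6-10), the control arm drifts 0 to +3 mmHg, and there are one or six checks. A true 5 mmHg becomes 3.2-4.4, and a true 8 mmHg becomes 5.5-7.1. With one check, 22-43% of controls and 9-28% of intervention participants are removed. With six checks it is 57-84% and 43-75%.

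**6. No true effect.** In the second model with one check and within-person SD 6, removal is 21.9% in each arm and the difference among those kept is 0.02 mmHg, which is simulation noise.

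**7. Numbers left, one check, 48 per arm.** Second model: 48·(0.78 + 0.91) = 81 down to 48·(0.57 + 0.72) = 62. Table above: 48·(0.95 + 0.99) = 93 down to 48·(0.71 + 0.83) = 74.

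**8. Why GEE does not help.** Standard GEE is valid when data are missing completely at random. Here the posttest is missing because a pressure reading was high. If the trigger is an interim reading outside the listed data collection, the information that explains the loss may not be in the dataset.

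**The case against.** The rule reads as a safety measure, and treating a participant whose pressure has risen is a clinical matter that this point does not question. But treating someone does not require ceasing to measure or analyse them. A milder reading is that exclusion only stops the assigned programme. The wording is exclusion from the study, and no section retains these participants. If the milder meaning was intended, the sentence still needs the same correction.

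The objection that the effects are conditional stands. Unequal removal and bias in the difference arise only if the arms differ in pressure or in detection. With no true effect and equal detection, the difference is essentially unbiased. The size also depends on inputs that the protocol does not give. A larger control fall or a baseline nearer 140/90 brings the loss down to about 8%.

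Four stronger readings are tempting, and the document does not support them:

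- **That the posttest reading itself triggers removal.** The protocol does not say which reading does. An interim check is equally possible.
- **That monthly health-centre access makes detection more frequent among controls.** The Control Group Arm section says such services can be accessed, but nothing bars the intervention arm from them.
- **That participants who do not follow the diet are also removed.** Limitations of the Study says only that "some participants may drop out of this study for various reasons, such as noncompliance with the consumption of a PBD". This is an expected limitation, not a removal rule.
- **That the rule could manufacture a benefit.** In the models run with equal detection, it pulls a true effect toward zero and creates none where there is none.

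**Conclusion.** The point holds in conditional form. The protocol states a rule that removes randomised participants on the value of the main outcome, with the threshold immediately above the entry range, and the planned GEE does not correct for it. That much rests on the text alone.

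If the diet lowers pressure, the rule removes more controls and attenuates the effect. For a true 5 mmHg SBP difference the loss is roughly 8-37% (estimates of about 4.6 down to 3.1 mmHg), with fewer than 96 analysed. Under no true effect and equal detection, the between-arm bias is about zero, but the mean in each arm is still flattered because the highest readings are gone.

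Confidence is high on the existence of the rule and on the direction of the bias when there is a benefit and detection is equal. It is low on the exact size, which rests on assumed SDs, an assumed effect and an assumed number of checks.

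**What to change.** Leave the treatment decision with the doctor as written and change only the data rule. In the Intervention section, replace "the participant will be excluded from the study" with wording to this effect: the participant stays in follow-up, has the posttest blood pressure measured, and is analysed in the randomised arm whether or not treatment was started.

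In addition:

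- record the reading that triggered treatment and its date;
- report the number of treatment starts by arm;
- add a sensitivity analysis for readings taken after treatment began.

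The cost is one changed sentence, a few added ones, and one posttest reading on people already enrolled. The small downside is that some posttest readings will be on medication, which the sensitivity analysis addresses. The change should be made before enrolment, because missed posttest readings cannot be recovered.

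### Rounding blood pressure data to the nearest ten adds avoidable error to both main outcomes and moves values across the trial's own stage limits

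*Protocol article*

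**What the plan says.** All references are to Activity 3 (the randomized controlled trial) in the protocol article.

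- **Outcome Measures**: "The main outcome measures in this study are SBP and DBP". The same section also sorts SBP and DBP into JNC VIII categories.
- **Data Collection Plan**: blood pressure is measured at least twice, with a third reading if the first two differ by 10 mmHg or more. Then "The 2 measurement values with the smallest difference will be averaged to obtain the final value".
- **Intervention**: "For blood pressure data, we will use rounded values, with values ending in 0-4 being rounded to" the ten below. The worked example is "120-124 mmHg will be rounded to 120 mmHg, 125 mmHg will be used directly, and 126-130 mmHg will be rounded to 130 mmHg". The sentence names no purpose to which the rule is limited, and no reason is given for it.
- **Inclusion and Exclusion Criteria**: entry requires "stage I hypertension (systolic blood pressure [SBP]: 140-159 mmHg and diastolic blood pressure [DBP]: 90-99 mmHg) according to the JNC VIII criteria", and the exclusions include "those with hypertension of stage II or higher".
- **Intervention**, just before the rounding rule: "If the blood pressure increases to hypertension stage II or above, appropriate treatment will be provided by the medical doctor in the PHC". That person then leaves the study.
- **Data Analysis Plan**: SBP and DBP at pretest and posttest are compared with a linear generalized estimating equation.

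**The concern.** The plan takes care to obtain a good blood pressure value and then coarsens it to steps of mostly 10 mmHg before using it. Two consequences follow.

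First, a continuous primary outcome gets extra measurement error at both time points, with no offsetting gain.

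Second, the stage limits fall just above blocks of four values that the rule pushes upward. A categorical reading of the outcome therefore changes with the rounding. If the same rounded values also drove entry or removal, people measured within the stage I range would be handled as stage II, and after randomization that would depend on the outcome itself. The article does not say which value those two rules use.

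**Working it through.** **Inputs.** The rounding rule and its example (Intervention); the stage I limits of 140-159 and 90-99 mmHg (Inclusion and Exclusion Criteria); the averaging rule (Data Collection Plan); the total of 96 participants (Sample Size Determination). Stage II from 160 or 100 mmHg is implied by the stage I upper limits and is not printed. No SD is given, so SDs below are assumptions. The order of averaging and rounding is not stated; I apply the rule to the final averaged value.

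**1. Reproduce the plan's example.** Coding the rule by last digit (0-4 down, 5 kept, 6-9 up) gives 120-124 → 120, 125 → 125, 126-130 → 130. This matches the article.

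**2. Size of the rounding error.** For last digits 0 to 9 the error (rounded minus measured) is 0, −1, −2, −3, −4, 0, +4, +3, +2, +1. With equally likely digits:

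- mean = 0
- variance = (0+1+4+9+16+0+16+9+4+1)/10 = 60/10 = 6 mmHg²
- SD = √6 = 2.45 mmHg

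**3. Effect on precision.** Variance inflation is 1 + 6/SD² for a single time point. For a change score, with independent errors at the two times, it is 1 + 12/variance.

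- Posttest variance 100: 1.06, and √1.06 = 1.03, so about 3% on the standard error.
- Change-score variance 100: 1.12, and √1.12 = 1.06, so about 6% on the standard error.

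The range for a posttest comparison, assuming 48 per arm, two-sided α of .05 and a difference that would give 80% power without rounding:

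| Assumed SD (mmHg) | Variance inflation | Power with rounding |
|---|---|---|
| 5 | 24% | 71% |
| 6 | 17% | 74% |
| 8 | 9% | 76% |
| 10 | 6% | 78% |
| 15 | 3% | 79% |
| 18 | 2% | 79% |

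These come from applying the rule to a discretized normal distribution. The shift in the mean was at most about 0.02 mmHg, so the error is essentially unbiased.

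**4. Individual changes.** A change from 154 to 156 (2 mmHg) is recorded as 150 to 160, that is 10 mmHg. A change from 146 to 154 (8 mmHg) is recorded as 150 to 150, that is 0.

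**5. Category limits.**

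- 156, 157, 158, 159 → 160: 4 of the 20 integer stage I SBP values.
- 96, 97, 98, 99 → 100: 4 of the 10 integer stage I DBP values.
- 136-139 → 140 and 86-89 → 90: values below stage I enter it.

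All four limits (140, 160, 90, 100) are multiples of ten, and rounding down stops at the multiple of ten. No value can therefore cross a limit downward, and every category error is upward. These are counts of possible values, not shares of participants.

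**6. Gap in the rule.** The mean of an odd and an even reading ends in .5. A value of 124.5 lies between the 120-124 band and 125, and 125.5 lies between 125 and the 126-130 band. The rule assigns neither.

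**The case against.** The strongest reply is that the certain harm is modest. The error averages to about zero and falls on both arms alike, so it does not materially bias the comparison of means. At an SD of 10 mmHg or more, the power loss in the table is about 1 to 2 points. Only narrow SDs give a marked loss, and the article does not tell us the SD. That stands, and it limits the point to avoidable imprecision and shifted categories.

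A reader might infer more: that the rule wrongly excludes many farmers at entry or removes many during follow-up. The documents do not support this as a fact. The entry criteria do not mention rounding. The stage II removal rule comes before the rounding sentence and does not refer to it. The Data Collection Plan calls the average of the two closest readings the final value. Upper limits of 159 and 99 also sit oddly with rounded data, which can end only in 0 or 5; this suggests that measured values were meant. On the other side, the rounding sentence has no exemption and follows directly on the statement that data are obtained at registration, pretest and posttest. Wrongful exclusion is therefore a risk left open by the wording. How many people it would affect cannot be derived, because the article gives no blood pressure distribution.

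The .5 gap is a minor drafting matter that any single convention would settle.

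**Conclusion.** The point holds in limited form. If the rule is followed, each SBP and DBP value carries an added error of variance 6 mmHg², assuming equally likely last digits and rounding of the final value. With an assumed variance of 100, this costs about 3% on the standard error for posttest values and about 6% for change scores; the cost grows as the SD narrows. JNC VIII categories would be shifted upward for 4 of 20 stage I SBP values and 4 of 10 stage I DBP values, provided that the categories are taken from rounded data. For entry and removal the finding is an ambiguity, not a demonstrated error. The validity of the between-arm comparison of means is not threatened by the rounding itself. The change is still worth making, because the loss buys nothing and the remedy is essentially free.

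**What to change.** 1. Delete the rounding rule for recorded and analysed blood pressure. Record every reading as measured.
2. Use the unrounded average defined in the Data Collection Plan for the SBP and DBP analysis and for JNC VIII categorization. Round only when displaying results in tables. This also removes the .5 gap.
3. Reconcile the Inclusion and Exclusion Criteria, the Data Collection Plan and the Intervention section so that they state which value, measured or rounded, feeds eligibility and the stage II removal. That choice is for the sponsor and investigators; what matters here is that it is stated once and applied consistently.

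The cost is one deleted sentence and a short clarification, with no extra measurements. It should be done before data collection, since readings that were stored only in rounded form cannot be recovered.
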